## Abstract

**Background:**

Osteoporosis affects over 200 million people worldwide at a high cost to healthcare systems. Although guidelines on assessing and managing osteoporosis are available, many patients are not receiving appropriate diagnostic testing or treatment. Findings from a systematic review of osteoporosis interventions, a series of mixed-methods studies, and advice from experts in osteoporosis and human-factors engineering were used collectively to develop a multicomponent tool (targeted to family physicians and patients at risk for osteoporosis) that may support clinical decision making in osteoporosis disease management at the point of care.

**Methods:**

A three-phased approach will be used to evaluate the osteoporosis tool. In phase 1, the tool will be implemented in three family practices. It will involve ensuring optimal functioning of the tool while minimizing disruption to usual practice. In phase 2, the tool will be pilot tested in a quasi-experimental interrupted time series (ITS) design to determine if it can improve osteoporosis disease management at the point of care. Phase 3 will involve conducting a qualitative postintervention follow-up study to better understand participants' experiences and perceived utility of the tool and readiness to adopt the tool at the point of care.

**Discussion:**

The osteoporosis tool has the potential to make several contributions to the development and evaluation of complex, chronic disease interventions, such as the inclusion of an implementation strategy prior to conducting an evaluation study. Anticipated benefits of the tool may be to increase awareness for patients about osteoporosis and its associated risks and provide an opportunity to discuss a management plan with their physician, which may all facilitate patient self-management.

## Background

There are over 200 million people worldwide who have osteoporosis, representing a considerable healthcare and financial burden [1-5]. The disease burden will be further compounded by an increasingly aging population, which will likely lead to more people who will suffer from osteoporosis [2,3,6]. The clinical consequence of osteoporosis is fragility fractures; vertebral and hip fractures have the most devastating prognosis [7] and are associated with an increased risk of death [8]. Furthermore, these fractures can significantly impair quality of life, physical function, and social interaction and can lead to admission to long-term care [9-11]. Although guidelines are available for osteoporosis disease management [12-14], many patients are not receiving appropriate diagnostic testing or treatment [15-19]. Clinical decision support systems (CDSSs) may be one solution to closing these practice gaps because they can provide evidence at the point of care to facilitate disease management. CDSSs work by generating patient-specific assessments or recommendations for clinicians; software algorithms match pieces of information from a knowledge database to relevant clinical data [20-22].

To determine what features of osteoporosis tools support clinical decision making in osteoporosis disease management, we conducted a systematic review of randomized controlled trials [23]. Findings showed that interventions consisting of reminders and education targeted to both physicians and patients were more promising for increasing osteoporosis investigations and treatment than single-component or single-target interventions [23]. We first developed a conceptual design for an osteoporosis disease-management tool using these findings and input from clinicians and experts in information technology and human-factors engineering. We then built a prototype using findings from a qualitative study of focus groups with family physicians [24]. The prototype was further refined in a series of usability studies with its target end users (physicians and patients at risk for osteoporosis) [25]. The osteoporosis tool is targeted to family physicians, and patients at risk for osteoporosis (women age ≥50 years, men age ≥65 years) and consists of three components: (1) a short (three to five minutes) electronic risk assessment questionnaire (RAQ) targeted to at-risk patients to be completed on a touch-screen tablet PC in the clinic examination room (while they wait for their physician); (2) a one-page best practice recommendation prompt (BestPROMPT) outlining appropriate osteoporosis disease-management recommendations (*e.g.*, to initiate bone mineral density [BMD] testing and osteoporosis treatment) customized according to patients' RAQ responses and available to physicians in the few minutes before the visit; (3) and a one-page, customized osteoporosis education (COPE) sheet tailored to patients' RAQ responses and given at the end of their physician visit. The functional osteoporosis tool is accessible online at http://knowledgetranslation.ca/osteo_final/index.html.

The objectives of the current study are to implement the osteoporosis tool prototype in three family practice settings and to conduct a pilot evaluation study to test the impact of the osteoporosis tool on disease management (*i.e.*, appropriate initiation of osteoporosis investigations and medications) using the quasi-experimental ITS design. Specifically, we will answer the following questions: (1) Does use of an osteoporosis disease-management tool by family physicians lead to enhanced osteoporosis management according to current clinical practice guidelines, as measured by increased BMD testing and prescription of osteoporosis medications such as bisphosphonates?; (2) How do clinicians perceive the utility of the tool for changing clinical practice and knowledge uptake?; (3) What is the impact of the tool on clinician adoption and satisfaction with the tool?; (4) Do family physicians use the tool in similar ways across different practice settings (*e.g.*, solo practice vs. group practice)?

## Methods

The osteoporosis tool will be evaluated according to a three-phase process (see Figure 1): implementation of the osteoporosis prototype in three family practices (phase 1), evaluation of the tool using an ITS design (phase 2), and a qualitative evaluation to identify the barriers to using the tool in practice (phase 3).

**Figure 1 F1:**
[figure not shown]
**The osteoporosis tool will be evaluated according to a three-phase process**: implementation of the osteoporosis prototype in three family practices (phase 1), evaluation of the tool using an ITS design (phase 2), and a qualitative evaluation to identify the barriers to using the tool in practice (phase 3).

### Phase 1: implementation of the osteoporosis tool

The tool will be implemented in three family practice settings selected purposively from the Hamilton Family Health Team (FHT). This is the largest of the 150 approved primary care FHTs in Ontario, Canada, serving approximately 250,000 people [26]. It includes a comprehensive team of healthcare professionals, including 129 family physicians, 114 nurses and nurse practitioners, 20 registered dieticians, 77 mental health counsellors, 22 psychiatrists, and 7 pharmacists. A unique feature of this FHT is that all physicians use an electronic patient record system, although not every physician uses the same system [26]. We purposively selected three family practices (two solo and one group practice) that used the same electronic medical record (EMR) system (*i.e.*, PracticeSolutions^® ^[Practice Solutions, Ottawa, Ontario, Canada]) to facilitate implementation of the osteoporosis tool and subsequent data collection during the evaluation study.

To ensure optimal functioning of the prototype and to minimize disruption to usual practice, the osteoporosis tool will be tailored to the practice and workflow of each practice setting. We will complete a workflow analysis in these family practice settings to ensure the prototype's optimal functioning, minimize the disruption of the tool on usual practice, and determine if the tool could be used by patients and physicians at the point of care. Our previous work revealed that workflow differences needs to be considered during the tool design process [24,25], particularly for complex interventions that are delivered at the point of care.

First, we will perform a workflow analysis, which will include observation of clinic staff during "typical" clinic days. Two researchers will document the patient registration process (particularly how patients are moved from the waiting area to the examination room) and estimate the average time that patients wait for their physician, the length of patient visits, and time between visits. Second, researchers and an information technologist will conduct an environmental scan to ensure appropriate equipment installation. Third, a procedures manual will be developed and customized for each site. Lastly, clinic staff (including physicians, nurses, and receptionists) will be trained on how to use and troubleshoot the osteoporosis tool. Once programming is completed and equipment installed, clinics will be instructed to begin using the tool, and observed to correct unanticipated installation, programming, or workflow interruption problems. We will consider the tool as implemented when no new problems are reported for at least one week.

### Phase 2: pilot evaluation study

#### Study design

The osteoporosis tool will be evaluated in a pilot study using the quasi-experimental ITS design. Quasi-experimental designs such as the ITS are particularly strong alternatives to randomized controlled trials (RCTs) [27] and are considered a useful and pragmatic tool, particularly for pilot studies where initial evaluations of interventions and their refinement need to be done before the testing of the tool on a wider scale is justified [27,28]. Results from ITS studies can serve to inform the investigation of mediating factors (for example, if the intervention is found to be more effective at one site but not at another), and they allow for the statistical investigation of potential biases in the estimate of the effect of the intervention [27,28]. For example, this design can address secular trends (*i.e.*, the outcome may be increasing or decreasing over time), history (*i.e.*, there may be trends or seasonal/cyclical observations over time), random fluctuations with no discernable patterns, and autocorrelation (*i.e.*, the extent to which data collected close together in time are correlated with each other) [27].

#### Sampling and population

In ITS studies, sample size calculations are related to the estimation of the number of observations or time points at which data will be collected. According to Ramsey *et al.*'s quality criteria for ITS designs, at least 10 pre- and 10 post-data points would be needed to reach at least 80% power to detect a change (if the autocorrelation is >0.4) [27]. Since the current study is a pilot, it is not known what the autocorrelation might be or what effect size the intervention is likely to produce. We therefore decided to use a relatively large number of data points to ensure that any trend or seasonal differences can be detected: 52 data points per site (where one data point = two-week segment)--26 data points before the introduction of the intervention (equivalent to 12 months' worth of two-week segments) and 26 data points after the introduction of the intervention (two-week segments for 12 months). Participants will be family physicians practicing in a solo or group practice within the Hamilton FHT and their patients at risk for osteoporosis selected according to gender- and age-eligibility criteria (*i.e.*, women ≥50 years of age, men ≥65 years of age).

#### Outcomes

Primary outcomes will be the initiation of appropriate osteoporosis investigations (*i.e.*, BMD testing) and treatment (*e.g.*, bisphosphonates, nutritional supplements such as calcium and vitamin D) during a patient visit. "Appropriate" osteoporosis management is defined as the recommendations outlined in current clinical practice guidelines from Osteoporosis Canada [12] and is represented by a disease-management algorithm programmed into the osteoporosis tool. Secondary outcomes will include fractures, the reason for the visit, number of patients who successfully complete the RAQ (defined as an electronic log generated by the tablet PC from patient-initiated RAQs), the mean time for patients to complete the RAQ, and the mapping of an osteoporosis care model for patients who will complete the RAQ (*i.e.*, documentation of what physicians do during the visit and subsequent visits with patients). Chart review will also consist of extraction of site-specific data, including the number of age-eligible patients/practice who had at least one visit during the intervention period, the number of patients who are at risk for osteoporosis, and the mean number of patients who were seen by their family physician within a two-week segment.

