#### Unit of analysis and data collection

Our unit of analysis will be based on the multiple baseline assessment of individual family practice sites rather than a single group of participants being tested repeatedly before and after the introduction of the intervention. The data set at each time point will consist of patient charts, which will represent the "episode of care" used to extract outcome data for the study. To ensure the completeness and validity of the data set at each time point, we will apply the quality-control criteria of ITS designs by Ramsay *et al.*, which recommend that 80%-100% of the total number of episodes of care (*i.e.*, patient charts) be used in the data collection [27].

Once the intervention is implemented, data will be collected on all outcomes from electronic patient records (*i.e.*, PracticeSolutions^®^) and the touch-screen tablet PCs. The purpose of the pre-intervention chart review will be to establish a stable baseline of standard practice for each site. Visit-specific data (*e.g.*, initiation of osteoporosis disease management, reason for visit) will be collected bimonthly at each site by two researchers (MK and CM). To minimize the introduction of contamination that could bias results during this phase, all data collection techniques, procedures, and data collection forms will be standardized. For calibration of reliability, these two researchers will extract data from 10 randomly selected patient charts in duplicate until their agreement reaches ≥80%, at which point they will abstract data independently. The two researchers will collect data from the touch-screen tablet PCs, which will automatically generate two electronic logs each time a patient completes the RAQ. The first log will outline dated/timed RAQ responses, and the other will summarize the content of the BestPROMPT sheet. These electronic logs will be matched against patient-visit chart data to verify the use of the tool during the visit and to map any actions taken by the physician in response to the use of the RAQ.

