### Potential limitations

Our study has several potential limitations. The ITS methodology, which was chosen for the pilot evaluation of the osteoporosis disease-management tool, is susceptible to several potential threats to internal validity. In general, we designed our methodology according to the ITS quality criteria recommended by Ramsay *et al. *to help overcome these threats and to rule out any alternative explanations of our findings [27]. Instrumentation (a threat to internal validity that could occur if the measurement method changes during the intervention and evaluation period) is a common threat in medical record data research, particularly in a multisite study. To overcome this problem, we will ensure that our databases, recording systems, observers, and outcome-measure instruments remain consistent, and they will be monitored closely for any changes that might occur over the course of the study. History is another potential threat because a change in clinical practice independent of the introduction of the intervention may occur from the influence or participation of other events and activities during the study period. For healthcare professionals and physicians in particular, these include continuing professional development activities (*e.g.*, participation in CME activities such as didactic lectures, small-group workshops, and attendance at conferences). To address this potential threat, we will collect information on continuing professional development activities using the demographic/evaluation questionnaire, which will incorporate questions targeted specifically for capturing clinical practice-related activities and events that might account for changes between baseline and postintervention observations.

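### As worded, the plan lets questionnaire data enter the assessment of appropriate management only after go-live, contrary to its promise of consistent instruments

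*Protocol article*

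**What the plan says.** All references are to the protocol article.

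- **Outcomes (Phase 2).** The primary outcomes are initiation of appropriate investigations and treatment at a patient visit. Appropriateness is defined by the Osteoporosis Canada guideline, and this standard "is represented by a disease-management algorithm programmed into the osteoporosis tool".
- **Background.** The prompt sheet carrying the tool's recommendations is "customized according to patients' RAQ responses and available to physicians in the few minutes before the visit". The RAQ is one of the three components of the intervention.
- **Unit of analysis and data collection.** On the baseline: "The purpose of the pre-intervention chart review will be to establish a stable baseline of standard practice for each site". On every time point: "The data set at each time point will consist of patient charts". On the period after go-live: "Once the intervention is implemented, data will be collected on all outcomes from electronic patient records", and the sentence goes on to add the touch-screen tablets as a second source. The tablets are described as devices "which will automatically generate two electronic logs each time a patient completes the RAQ"; one log holds the RAQ answers and the other the content of the prompt sheet. The logs are to be matched to chart data to confirm that the tool was used and to trace what the physician did.
- **Potential limitations.** Instrumentation is named as a threat, with the assurance that "we will ensure that our databases, recording systems, observers, and outcome-measure instruments remain consistent".
- **Analysis.** Impact is the change in level between the baseline and postintervention periods. It is estimated for the primary outcomes by ARIMA and time-series regression.

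**The concern.** An interrupted time series attributes a step at go-live to the intervention. Anything else that changes at that moment is attributed to it too. Here the one operational criterion given for the primary outcome sits inside the intervention and runs on data that the intervention creates. In the baseline year, appropriateness can be assessed only from the risk factors that charts happen to record. After go-live, a structured risk profile and a ready-made statement of what was recommended exist for RAQ completers, and the text permits their use for all outcomes.

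If they are used, ascertainment of the primary outcome changes at the interruption. The Analysis section credits ARIMA with handling trend, seasonality and random error. A change in ascertainment at go-live is none of these, and more time points only estimate it more precisely.

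**Working it through.** **The plan's own figure.** 26 + 26 = 52 points per site, and 26 × 2 weeks = 52 weeks per phase. This reproduces and is not in dispute. The document gives no figure for ascertainment, so every rate below is an assumption used for illustration.

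**Step 1: availability of information by period.**

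| Information | Baseline | After go-live, RAQ completed | After go-live, RAQ not completed |
|---|---|---|---|
| BMD order or prescription in chart | yes | yes | yes |
| Risk factors recorded in chart | yes, as documented | yes, as documented | yes, as documented |
| RAQ answers and prompt-sheet log | none | yes | none |

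The first row is the same throughout, so initiation itself is not exposed. Only the appropriateness assessment, or a denominator based on it, can draw on the third row.

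**Step 2: numerator effect, with all age- and sex-eligible visits as denominator and no change in practice.** Let c be the share of truly appropriate initiations that charts allow one to classify (the same in both periods), and u the share of those patients with a completed RAQ. Assume the RAQ classifies all of them. The ratio of measured rates, post to pre, is [u + (1 − u)c] / c.

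| u | c = 0.8 | c = 0.6 |
|---|---|---|
| 1.0 | 1/0.8 = 1.25 | 1/0.6 = 1.67 |
| 0.5 | 0.90/0.80 = 1.125 | 0.80/0.60 = 1.33 |
| 0.3 | 0.86/0.80 = 1.075 | 0.72/0.60 = 1.20 |

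The first row needs complete RAQ uptake. The document does not assume that, because it counts RAQ completion as a secondary outcome.

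**Step 3: chance of a false signal.** Assume 40 charts per segment, so 26 × 40 = 1,040 per phase, independent visits, a true rate of 10% in both phases, full capture afterwards and a simple two-sided 5% comparison of two proportions.

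- Charts capture 90%: 9% against 10%. The standard error is √[(0.09×0.91 + 0.10×0.90)/1040] = 0.0129, z = 0.78, and the probability of rejection is about 0.12.
- Charts capture 70%: 7% against 10%. The standard error is √[(0.07×0.93 + 0.10×0.90)/1040] = 0.0122, z = 2.46, and the probability is about 0.69.

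**Step 4: denominator effect.** Now let the denominator be patients with an indication, with 25% truly initiated in both phases and full capture afterwards. If charts identify a share s₁ of initiated and s₀ of non-initiated indicated patients, the baseline reads 0.25s₁ / (0.25s₁ + 0.75s₀).

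- s₁ = 0.9, s₀ = 0.5: 0.225/0.600 = 37.5%, a spurious fall of 12.5 points.
- s₁ = 0.9, s₀ = 0.7: 0.225/0.750 = 30.0%, a fall of 5.0 points.
- s₁ = 0.95, s₀ = 0.9: 0.2375/0.9125 = 26.0%, a fall of 1.0 point.

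The sign therefore depends on how the measure is built. With the same ascertainment in both periods, the artefact is zero in every case.

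**The case against.** The strongest reply is that the text, taken as a whole, points to charts. Appropriateness is defined by an external guideline, which the algorithm only represents, and a guideline can be applied to a chart without a RAQ. Charts are named as the data set at each time point. The logs have a stated role in verification and mapping, and the Analysis section sends them to descriptive analysis, apart from the ARIMA models. The sentence on all outcomes can be read distributively, since RAQ completion and completion time can come only from tablets. Collection forms are to be standardized, and research question 1 in the Background speaks simply of BMD testing and prescribing. A condensed article may also leave the abstraction rule to a fuller document.

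Most of this stands. A reader might infer that outcomes before and after go-live are in fact measured with different instruments. The document does not support that: nowhere does it say that appropriateness after go-live is scored from RAQ answers. Nor does it support a rise of 25% to 67% as an expected bias, because that range rests on invented capture rates and complete uptake.

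The reply does not remove the conflict. The article does fix an operational criterion and does state sources by phase, and taken literally those statements do not fit the assurance of consistent instruments. A standardized form cannot supply RAQ answers that were never collected.

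**Conclusion.** The concern holds as an exposure, not as a demonstrated bias. The Outcomes and data-collection sections, read literally, allow RAQ data into the appropriateness assessment only after go-live, and this conflicts with the commitment in Potential limitations. If it happened, the result would be a step coinciding with the intervention that the planned models cannot separate from a true effect.

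Its size and direction cannot be determined from the document. Under the stated assumptions it runs from slight (a ratio of 1.075, or a fall of 1 point) to enough to produce a false finding more often than not (probability about 0.69). Counts of BMD tests and prescriptions are not affected by the source change. Because the primary pre/post comparison depends on the point and the remedy is cheap, it should be settled before abstraction of the postintervention period.

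**What to change.** Reconcile Outcomes, Unit of analysis and data collection, and Potential limitations by stating the following:

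1. The primary outcomes are extracted from chart or electronic-record fields available in both periods, for every age- and sex-eligible visit.
2. Appropriateness is assessed by one chart-only rule derived from the guideline. It is applied identically before and after go-live, whether or not the patient completed the RAQ. The content of the rule is for the investigators to set.
3. Raw initiation per eligible visit, in line with research question 1, is reported alongside. This is needed because the tool may also change how fully risk factors are charted, which even a chart-only rule would pick up.
4. The text says how calcium and vitamin D supplements are captured, since Outcomes counts them as treatment while research question 1 names prescriptions.
5. Tablet and RAQ data serve only uptake, process and post-only descriptive outcomes, including any appropriateness measure based on the algorithm.

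The cost is revised outcome wording and an adjusted abstraction form; no new data source is needed. The downside is that a chart-only rule is coarser than the RAQ algorithm and will leave some visits unclassified, but it does so by the same rule in both periods.
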